### Data management {19}

All data will be retrieved from electronic patient records at the time of hospitalization and then at the follow-up visit and collected in a dedicated anonymized datasheet. Informed consent and end-of-trial dates will be recorded in the electronic patient dossier, and signed paper forms will be stored within each hospital in a locked room, whose keys will only be available to the research team and will be safeguarded by the principal investigator.

### Confidentiality {27}

Research data will be stored using a study identification code for each participant. The key to the identification code list will only be available to the research team during the study and will be documented and safeguarded by the principal investigator according to research guidelines after completion of the study. No patient identification details will be reported in publications.

Data collection and management will be in accordance with the EU regulation 2016/679, the Privacy Code (D.lgs 196/03 s.m.i) and Guide Lines of 24th July 2008, and will be guaranteed by the promoter of the study. The promoter will store the original paper documentation (i.e. informed consent) for at least 7 years in compliance with LD 200/2007.

### Plans for collection, laboratory evaluation and storage of biological specimens for genetic or molecular analysis in this trial/future use {33}

Not applicable. Collection, laboratory evaluation and storage of biological specimens for genetic or molecular analysis are not included in the study.

### Statistical methods

#### Statistical methods for primary and secondary outcomes {20a}

Demographic and clinical characteristics will be presented as percentage in case of ordinal variables and as percentages, means, medians and standard deviations and/or interquartile range in case of categorical and/or quantitative variables. The Pearson *χ*^2^ and the *H*-test by Kruskal-Wallis will be used for any assessment of differences between the three groups. To evaluate the primary endpoint of the study, the Mann-Whitney test will be used for comparisons between groups with an alpha equal to 0.01667. The Mann-Whitney test will also be used to evaluate the secondary endpoint obtained by AUC, while the Pearson *χ*^2^ will be used to compare the proportion of cases above and below the serum lactate peak cut-off > 3mmol. To compare the secondary endpoints in the three groups according to the types of variables, ANOVA or non-parametric *H*-test by Kruskal-Wallis will be used for quantitative variables, while the Pearson *χ*^2^ test will be performed for dichotomous or categorical variables. ANOVA for repeated measures, or Friedman test or the mixed effects model will be used for variables collected at different timepoints. A *p*-value < 0.05 will be considered statistically significant. Both an intention to treat (ITT) and per protocol (PP) analysis will be performed.

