- Intraoperative (postoperative day, POD, 0)A continuous monitoring of blood pressure will be performed invasively by cannulating the radial or femoral artery, as is customary in cardiac surgery. Data of MAP will be recorded at the beginning of CPB, every 20 min until minute 300 and at the end of CPB.ABG after orotracheal intubation, at the beginning of CPB, every 20 min during CPB (eventually until minute 300), at the end of CPB, at the end of surgery. Data collected: lactates as organ perfusion index, Hb and Hct.Real-time and continuous monitoring of respiratory gases during CPB suggestive of the perfusion trend, through CDI ® 550 Blood parameter monitoring system (Terumo Europe) [25], data collection related to oxygen delivery (DO_2_), oxygen consumption (VO_2_) and oxygen extraction (O_2_ER), at the beginning of CPB, every 20 min (until minute 300) and at the end of CPB.Intraoperative monitoring of Near-Infrared Spectroscopy NIRS [26] defined as non-invasive measurement of cerebral microcirculatory blood flow. Data will be collected at anaesthesia induction, before skin incision, at the beginning of CPB, every 20 min (until minute 300), at the end of CPB and at the end of surgery.Monitoring of CPB and aortic cross-clamp timesCalculation of “vasoactive inotropic score” (VIS) [22] which relates the entity of inotropic and or vasoactive support. VIS max is obtained through the following calculation: [Dopamine dose (mcgkg/min)+ Dobutamine dose (mcg/kg/min) + 100 × Epinephrine dose (mcg/kg/min) + 50 × Levosimendan dose (mcg/kg/min) + 10 × Milrinone dose (mcg/kg/min) + 10,000 × Vasopressin dose (units/kg/min) + 100 × Norepinephrine dose (mcg/kg/min)]. The VIS will be calculated according to the length of surgery.Monitoring of nitroglycerine dose during surgery

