### Outcomes {12}

#### Primary outcome

The primary endpoint of the study is the serum lactate peak (Lmax) (mmol/l) detected during CPB. The mean of this value will be compared between the three groups of treatment.

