### Sample size {14}

The sample size has been calculated for the primary endpoint: the maximum serum lactate value (Lmax). A preliminary analysis was performed on a sample size of 128 consecutive patients undergone to elective cardiac surgery at Cardiac Surgery Division at AOUI of Verona (about the 10% of the annual volume cases at our Institution). All patients were treated with standard MAP (standard of care) and the estimated mean of Lmax during CPB was 1.25 mmol/l, with a standard deviation of 0.7 mmol/l. Starting from this value, a reduction of −15% of the mean Lmax was considered clinically significant for every comparison that will be performed in the study, as listed below:Standard MAP vs High MAP (−15%) difference *d*=−0,19Standard MAP vs patient-tailored MAP (−15%) difference *d*=−19High MAP vs patient-tailored MAP (−15%) difference *d*=−19

Based on these assumptions, performing the Mann-Whitney non-parametric test and considering an alpha of 0.05 s. Bonferroni for all the three comparisons (corrected Alpha= 0.01667) and a power of 80%, 300 patients should be enrolled for each group, for a total of 900 patients (PASS 14). To account for a potential drop-out of 10%, the size becomes 333 patients per group, then a total of 999 patients. The number of patients that each Participating Centres should recruit has been calculated based on the annual cases volume of each Centre, as follows:

Cardiac Surgery Division of AOUI Verona: 327 cases (109 per group)Cardiac Surgery Division of Ospedale Maggiore di Parma: 162 cases (54 per group)Cardiac Surgery Division of Azienda Sanitaria Universitaria Friuli Centrale di Udine: 231 cases (77 per group)Cardiac Surgery Division of Hospital Clinic de Barcelona, Spain: 279 cases (93 per cases)

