## Assignment of interventions: allocation

### Sequence generation {16a}

The list of randomization will be generated for each centre using STATA statistical software 14, by the Clinical Research Unit of Azienda Ospedaliera Universitaria Integrata of Verona. The balanced block randomization method will be used. To reduce predictability of a random sequence, details of any planned restriction will be provided in a separate document that is unavailable to those who enrol participants or assign interventions

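### The primary test of Lmax is an unadjusted rank comparison: it leaves centre and pre-CPB lactate unused and gives no estimate on the mean scale on which endpoint and target effect are defined

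*Protocol article*

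**What the plan says.** All references are to the protocol article.

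- Statistical methods {20a}: "To evaluate the primary endpoint of the study, the Mann-Whitney test will be used for comparisons between groups with an alpha equal to 0.01667". For this endpoint the section names no centre term, covariate, effect measure or confidence interval.
- Primary outcome, on peak lactate during bypass: "The mean of this value will be compared between the three groups of treatment".
- Sample size {14}: in the preliminary series, "the estimated mean of Lmax during CPB was 1.25 mmol/l, with a standard deviation of 0.7 mmol/l". A 15% reduction "of the mean Lmax was considered clinically significant for every comparison that will be performed in the study", which the article prints as 0.19 mmol/l. The calculation is for a Mann-Whitney test. Its significance level is described as "Bonferroni for all the three comparisons (corrected Alpha= 0.01667". The resulting group size, before allowance for drop-out, appears in the same sentence: "a power of 80%, 300 patients should be enrolled for each group, for a total of 900 patients".
- Sequence generation {16a}: "The list of randomization will be generated for each centre using STATA statistical software 14", with balanced blocks. Randomisation is therefore stratified by centre, with four centres.
- Procedures: an arterial blood gas on the day before surgery records preoperative lactate. The intraoperative schedule is "ABG after orotracheal intubation, at the beginning of CPB, every 20 min during CPB". Two lactate values thus precede the start of the pressure strategy.

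**The concern.** Two things do not fit together.

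First, the endpoint and the clinically relevant effect are stated as means, but the test compares ranks. Mann-Whitney addresses whether values in one arm tend to exceed those in the other. It coincides with a comparison of means under a pure shift, but not in general when the outcome is skewed and the spread differs between arms. With SD 0.7 on a mean of 1.25, the mean minus two SDs is 1.25 − 1.40 = −0.15, which is impossible for a concentration, so right skew is likely. A significant rank test would not by itself show whether the 15% reduction in the mean was reached.

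Second, the design stratifies by centre and the schedule supplies a baseline for the same quantity, yet the named test uses neither. Variation due to centre and starting lactate stays in the error term, and a chance imbalance in starting lactate stays in the primary comparison.

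**Working it through.** **Inputs.** From Sample size {14}: mean 1.25, SD 0.7, d = 0.19 (unrounded 0.15 × 1.25 = 0.1875), alpha 0.05/3 = 0.01667, power 80%, 300 per group. The sidedness is not stated; two-sided is assumed because it reproduces the plan's figure. The normal quantiles are 2.394 and 0.842. The article does not give the share of Lmax variance explained by centre and baseline lactate (R²), so a range is assumed.

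**1. The plan's own figure.**
- Two means: n = 2 × [0.7 × (2.394 + 0.842)/0.19]² = 284.2, so 285 per group.
- Mann-Whitney under normality: 284.2 × π/3 = 297.6, so 298. The t-based version gives 299.5, so 300.
- With d = 0.1875: 306, or 308 t-based. A one-sided test gives about 251 and does not match.

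The stated 300 reproduces.

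**2. Power at 300 per arm under normality, d = 0.19.**
- Planned Mann-Whitney: effective n = 300 × 3/π = 286.5. Then 0.19/(0.7 × √(2/286.5)) − 2.394 = 0.855, giving 80.4%.
- Linear model: power = Φ(0.19/(0.7 × √(1 − R²) × √(2/300)) − 2.394).
  - R² = 0: Φ(3.324 − 2.394), 82.4%.
  - R² = 0.10: Φ(3.504 − 2.394), 86.7%.
  - R² = 0.25: Φ(3.839 − 2.394), 92.6%.
- In patients, explaining 10% or 25% of the variance is worth 1/0.90 = 1.11 or 1/0.75 = 1.33 times the sample.

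**3. Effect of ignoring centre alone.** Simulation with normal data, four centres in the planned proportions and 2,000 runs per setting; the centre shares of variance are assumed.

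| Centre share | Type I error, Mann-Whitney | Type I error, van Elteren | Power, Mann-Whitney | Power, van Elteren |
|---|---|---|---|---|
| 0% | 0.015 | 0.017 | 80% | 80% |
| 5% | 0.014 | 0.016 | 81% | 83% |
| 10% | 0.011 | 0.017 | 82% | 85% |
| 20% | 0.006 | 0.015 | 83% | 89% |

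Against a nominal 0.0167, the unadjusted test becomes conservative.

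**4. Can the rank test and the mean disagree?** Assume log-normal Lmax, equal means of 1.25, 300 per arm and SD 0.7 in one arm. Mann-Whitney rejects about 16% of the time if the other SD is 0.9 and about 65% if it is 1.1. Welch's t-test rejects about 2% in both cases.

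A log-scale comparison has the same property: with SDs 0.7 and 1.1 it rejects about two thirds of the time. The geometric mean ratio is then √[(1 + 0.56²)/(1 + 0.88²)] = √(1.314/1.774) = 0.86, which would look like the planned 15% reduction although the means are equal.

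**5. Price of the mean scale under skew.** Assume a log-normal with mean 1.25 and SD 0.7, and a proportional 15% reduction. Simulated power is about 90 to 92% for Mann-Whitney, 92 to 93% on the log scale, and 88% for Welch on the raw scale. By normal approximation, the raw-scale standard error is √[(0.7² + 0.595²)/300] = 0.053 and 0.1875/0.053 = 3.53, giving 87% unadjusted. With R² = 0.10, 3.53/√0.90 = 3.73, giving 91%. Adjustment explaining roughly 10% of the variance thus about recovers what the raw scale gives up.

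**The case against.** The strongest case for the plan is this. The trial was sized for Mann-Whitney, so test, alpha and sample size agree. Skew makes a rank test a reasonable choice. Ignoring centre errs on the safe side, and randomisation balances baseline lactate in expectation. The trial is described as exploratory. The article condenses a fuller protocol, in which effect estimates, intervals and covariates may be specified. The gains from adjustment rest on correlations that nobody has supplied, and if these are near zero the gain is small.

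Most of that stands, and it rules out several stronger readings that a reader might infer:

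- That the sample size is wrong. It reproduces.
- That false-positive error is inflated. It is not; the unadjusted test is conservative when centres differ.
- That only p-values will be reported. The article's silence on estimates does not show this.
- That a log-scale model would lift power from 80% to 92%. Those figures rest on different distributions; under the same log-normal shift the rank test already has about 90 to 92%.
- That restating the endpoint as a geometric mean ratio would cure the mismatch. It would replace the stated mean with another quantity and, as step 4 shows, would be open to the same divergence.

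What does not fall away is that the article itself names the primary test. That test does not estimate the mean difference the same article sets as its target, and it uses neither the stratification factor nor a baseline already scheduled for collection.

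**Conclusion.** The point holds as one of efficiency and of aligning the analysis with the stated quantity; it is not a failure of validity. Under normality, with d = 0.19 and SD 0.7, replacing the planned test by an adjusted linear model takes power at 300 per arm from about 80% to 82%, 87% or 93% when centre and baseline lactate explain 0%, 10% or 25% of the variance. The 0% figure reflects only the rank test's efficiency under normality, and under log-normal skew that small advantage reverses. The divergence between rank test and mean requires unequal spread between arms. That is an assumption: the article gives an SD for standard MAP only. The more certain benefit is an estimate with an interval that can be set against 15%.

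**What to change.** Before database lock, and without looking at outcomes by arm:

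- Make the primary analysis a linear model for Lmax in mmol/l with arm, centre and one pre-CPB lactate value, with robust standard errors. Choose the post-intubation or the day-before value in advance. Do not use the sample at the start of bypass, which lies inside the window that defines Lmax.
- Report the three pairwise adjusted mean differences, also as a percentage of the comparator mean, with 98.33% confidence intervals, to be set against 0.19 mmol/l (15%).
- Keep the rank test as a sensitivity analysis, in its centre-stratified (van Elteren) form.
- Leave the primary outcome worded as a comparison of means; it then agrees with the analysis.

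No new data and no change in sample size are needed. The costs are a protocol amendment to the primary analysis in an open-label trial that has recruited since May 2021, best drafted by the blinded analyst, and somewhat less robustness to skew than a rank test, which the sensitivity analysis covers.

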## Procedures

### Preoperative

- Preoperative outpatient visit (7 days before surgery)Clinical evaluation of the patient and eligibility for the study through collection of anamnestic data and physical examination.

- Day before surgery:Collection of informed consent for participating the studyRandomizationMeasurement of preoperative MAP in every patient enrolled, regardless of the assignment group through randomization.Blood samples to assess: haemoglobin (Hb), haematocrit (Ht), white blood cells (WBC), platelets (Plt), C reactive protein (CRP), lactate dehydrogenase (LDH), prothrombin time (PT/INR), activated partial thromboplastin time (aPTT), fibrinogen and creatinine (mg/dl), lipase, pancreatic amylase, alanine aminotransferase (ALT), aspartate aminotransferase (AST), total bilirubin (Bil Tot), conjugated bilirubin (direct Bil), unconjugated bilirubin (indirect Bil), gamma-glutamyltransferase (GGT), alkaline phosphatase (ALP) and albuminArterial blood gas test (ABG) to evaluate preoperative lactatemiaCalculation of eGFR (according to MDRD) to evaluate preoperative renal functionEvaluation of preoperative mRS in case of stroke in amnestic history.

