#### Secondary outcomes

The area under the curve (AUC) of the serum lactate values measured during CPBNumber of cases with serum lactate peak > 3 mmol/l during CPBEvaluation of intraoperative cerebral perfusion (through monitoring of NIRS)Intraoperative pulmonary perfusion (through Pa/Fi ratio, paO_2_, paCO_2_ at ABG and VO_2_R and DO_2_ of CDI)Evaluation of intraoperative and postoperative low cardiac output syndrome (through the calculation of VISmax)Postoperative and 30-day LVEF (%)Evaluation of pulmonary injury (through the LIS)Postoperative and 30-day Acute Kidney Injury (according to AKIN score)Postoperative gastrointestinal ischaemiaHepatic function and coagulation indexesEvaluation of neurological dysfunction (as dichotomous variable) and evaluation through mRS (0–6) in case permanent neurological injuryIn-hospital mortality and at 30 days from surgeryRe-hospitalization

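### Quantitative secondary outcomes (LVEF, liver and coagulation tests, NIRS) are given tests with no stated baseline term although pre-treatment values exist; adjusting for them would gain precision at almost no cost

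*Protocol article*

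**What the plan says.** The Statistical methods section {20a} of the protocol article fixes the tests by type of variable. For quantitative variables: "To compare the secondary endpoints in the three groups according to the types of variables, ANOVA or non-parametric" Kruskal-Wallis. For repeated measurements: "ANOVA for repeated measures, or Friedman test or the mixed effects model will be used for variables collected at different timepoints". The threshold is a p-value for which less than "0.05 will be considered statistically significant". No covariate, change score or baseline term appears in this section or elsewhere in the article.

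Each outcome considered here has a value from before the assigned MAP is applied:

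- **LVEF.** The outcome is "Postoperative and 30-day LVEF", measured on postoperative day 4 and at day 30. Eligibility requires a preoperative echocardiogram showing LVEF of at least 40%.
- **Liver and coagulation tests.** The panel drawn the day before surgery includes "prothrombin time (PT/INR), activated partial thromboplastin time (aPTT), fibrinogen and creatinine (mg/dl), lipase, pancreatic amylase, alanine aminotransferase (ALT" and further liver tests. Blood chemistry is repeated at ICU arrival and on postoperative days 1 and 4.
- **NIRS.** The intraoperative procedures state: "Data will be collected at anaesthesia induction, before skin incision, at the beginning of CPB", then every 20 minutes, at the end of bypass and at the end of surgery. The first two readings precede bypass, yet they stand in one series with the later ones.

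**The concern.** Patients differ in LVEF, laboratory values and cerebral oxygenation before bypass begins. If those differences persist, an analysis that ignores the baseline leaves them in the error term, and any chance imbalance stays in the estimate. A real effect of the MAP strategy on organ function is then harder to detect.

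NIRS raises a second question. The induction and pre-incision readings cannot be affected by a pressure target that applies only during bypass. Because {20a} does not say which readings are baseline and which are outcome, an analyst could average the arm effect over all of them and so shrink it.

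**Working it through.** **Number per arm.** The plan's only sample size is for Lmax, and it reproduces. Inputs from Sample size {14}: "estimated mean of Lmax during CPB was 1.25 mmol/l, with a standard deviation of 0.7 mmol/l", a difference of 0.19 mmol/l, alpha 0.01667 (taken as two-sided) and power 80%. A two-sample comparison of means needs 2 × (2.394 + 0.842)² × (0.7/0.19)² ≈ 285 per group. Multiplying by π/3 for the Mann-Whitney test with normal data gives 299, against 300 stated. Then 300/0.9 = 333.3, against 333 stated. So 300 is the evaluable number per arm and 333 the number recruited. No power is stated for any secondary outcome.

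**Single-time comparison of two arms.** The article gives no effect size or baseline correlation r for these outcomes; both are assumed. With standardised difference 0.2 and two-sided 0.05, power = Φ(0.2/√(1 − r²) × √(n/2) − 1.96). At n = 300, √150 = 12.25 and 0.2 × 12.25 = 2.449.

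| r | 2.449/√(1 − r²) | Power, n = 300 | Power, n = 333 |
|---|---|---|---|
| unadjusted | 2.449 | 69% | 73% |
| 0.3 | 2.568 | 73% | 77% |
| 0.5 | 2.828 | 81% | 85% |
| 0.7 | 3.430 | 93% | 95% |
| 0.8 | 4.082 | 98% | 99% |

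A three-arm check gives the same picture. For an effect that unadjusted ANOVA detects with 80% power at 300 per arm, adjustment gives 83.8%, 90.5%, 98.0% and 99.8% at these correlations.

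**Baseline kept as a timepoint.** LVEF and the laboratory tests are measured more than once, so the repeated-measures sentence may govern them. Take LVEF at three times (preoperative, day 4, day 30), an effect of 0.2 SD at both later times, equal correlation r between times, 333 per arm and two arms. The arm-by-time noncentrality is (333/2) × 0.04 × (2/3)/(1 − r) = 4.44/(1 − r) on 2 degrees of freedom. Power is about 76%, 86%, 94% and 99% at r = 0.5, 0.6, 0.7 and 0.8. The single-time adjusted figures are 85%, 90%, 95% and 99%, so the gap is 0 to 9 points. This pairing is not quite like for like, since the interaction uses both later readings and the adjusted figure only one. The mean of both later readings, adjusted for baseline, has variance (1 + r)/2 − r². At r = 0.5 that is 0.5, and power is Φ(0.2/√(2 × 0.5/333) − 1.96) ≈ 95%.

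**NIRS.** All inputs are assumed: between-patient SD 8, within-patient SD 4, nine readings of which five can carry the effect, 333 per arm.

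- *Arm effect averaged over all nine:* contrast 5/9 of the effect, variance 64 + 16/9 = 65.8. Power is 42% for a 2-point effect and 14% for 1 point.
- *Five on-bypass readings adjusted for the mean of the two pre-bypass readings:* variance (64 + 16/5) − 64²/(64 + 16/2) = 10.3. Power is about 100% and 98%.
- *Arm-by-time test:* noncentrality (333/2) × effect² × (20/9)/16 on 8 degrees of freedom, that is 92.5 and 23.1. Power is about 100% and 95%.

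With within-patient SD 6 and a 1-point effect, arm-by-time power is 60% and adjusted power 80%. With between-patient SD 6 instead of 8 (within-patient SD 4), the 42% becomes 65%.

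**The case against.** The strongest reply is that covariates and the choice of contrast normally belong in the SAP, which is not shown, and that the mixed model listed in {20a} could carry a baseline term. This stands in part: nothing in {20a} forbids one. But {20a} does choose tests, and ANOVA and Kruskal-Wallis as named carry no covariate. Friedman is a within-patient test and does not compare arms at all. Naming a better method is therefore a comment on what the article states, not a complaint about missing detail.

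A reader might infer from the NIRS series that the plan reduces power from nearly 100% to 42%. The documents do not support that. {20a} never says that an arm effect averaged over all readings will be tested, and the equally ordinary arm-by-time reading largely removes the gap. Nor are all four unaffected readings in that scenario pre-bypass: only two are, and dropping just those two raises 42% to 62%.

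A reader might also take NIRS to be the leading secondary outcome. It comes first under Secondary objectives, but the Secondary outcomes list puts lactate AUC and peak lactate above 3 mmol/l ahead of it, and no hierarchy is stated.

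It is also fair to say that unadjusted randomised comparisons are unbiased, that the trial calls itself exploratory, and that it was not sized for these outcomes. All of that stands and limits the weight of the point.

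**Conclusion.** The point holds as a modest loss of precision in secondary outcomes. Validity and the Lmax analysis are not in question. For a single-time comparison at 300 per arm, adjustment adds about 4 points of power at a baseline correlation of 0.3, 12 at 0.5, 24 at 0.7 and 29 at 0.8, from 69%. Against an arm-by-time test that already uses the preoperative value, the gain is roughly 0 to 9 points at correlations of 0.5 to 0.8 (333 per arm, in the pairing shown).

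For NIRS the dilution is conditional: it arises only if the arm effect is averaged over readings that include those taken before bypass. The article neither states nor rules this out.

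Every size here rests on assumed correlations, SDs and effects. If post-bypass values correlate weakly with baseline, or if the LVEF cut-off at 40% narrows its range, the benefit will be near the lower end. This is an optional improvement.

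**What to change.** In {20a}, state that quantitative secondary outcomes with a pre-treatment value will be analysed by ANCOVA (one time) or by a mixed model on post-treatment readings (several times), with the patient's own pre-treatment value as covariate. Name the covariates: preoperative LVEF, the preoperative laboratory value, and the mean of the induction and pre-incision NIRS readings. Keep the pre-bypass NIRS readings out of the outcome side. Use a log or rank transform where values are skewed.

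The cost is a few sentences and slightly more analysis work, with no added patients or procedures. The numerical preoperative LVEF must be in the dataset: the article uses it as an eligibility threshold but does not list it among the preoperative data collected. No interim analysis is planned and recruitment is expected to run to 31/12/2026, so the wording can be settled before the outcome data are analysed.

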### Postoperative

- POD at arrival in intensive care unit (ICU), POD 1 and 4Blood chemistry samplesCalculation of eGFR (according to MDRD)ABG at arrival in ICU, at 3–6–12–24 h after surgery. Data collection on serum lactates, pH, paO_2_, paCO_2_, BE, HCO_3_−, calculation of the Pa/Fi ratioChest X-ray and evaluation of eventual pulmonary damage through Murray “Lung Injury Score” (LIS) [23]. The score considers 4 criteria for the development of ALI/ARDS: hypoxemia, respiratory system compliance, chest radiographic findings and the positive expiratory pressure level. Each criteria receives a score from 0 to 4 according to the gravity of the condition. The final score is obtained dividing the collective score by the number of components used. A score equal to 0 shows the absence of pulmonary damage, a score between 1 and 2.5 shows a mild to moderate pulmonary damage and a final score major than 2.5 shows the presence of ARDS.Monitoring of estubation time (hours)Calculation of VISmaxMonitoring of postoperative cardiac function at POD 4 through echocardiogram and evaluation of LVEFMonitoring of postoperative stroke; a diagnosed stroke by a neurologist according to clinical, radiological (CT scan and/or MRI) and electrophysiological examination (EEG). Patients affected by stroke will undergo “modified Rankin Scale” (mRS) calculation which evaluates the degree of disability following a stroke and will be compared to the preoperative mRS. The score goes from a minimum score of 0 (no disability) to 6 (death).Evaluation of acute kidney injury according to the definition of “Acute Kidney Injury” (AKIN) [27] through a stratification of renal damage in three stages: [1] Creatinine × 1.5–2.0 from baseline or Creatinine increased by at least 0.3 mg/dl (26.5μmol/L) [2]; Creatinine × 2.0–2.9 from baseline [3]; Creatinine > 3.0 from baseline or Creatinine increased at least 4 mg/dl (353.6 μmol/l) or the initiation of dialysis.Monitoring of gastrointestinal ischaemia: a diagnosed ischaemia by a surgery consultant according to the value of serum lactate, WBC, clinical and radiological (CT scan and/or abdomen ultrasound) examination.Monitoring of in-hospital death

- Follow-up visit at 30 days from surgery:Stroke and eventual transitory or permanent neurological damage (mRS score)Acute kidney injury (eGFR and AKIN score)Cardiac function (LVEF)Re-hospitalizationDeath for cardiovascular or other causes.

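### The test-by-type rule names no order-respecting test for AKIN stage, so on its natural reading a staged AKI outcome goes to an order-blind 6-df chi-square

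*Protocol article*

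**What the plan says.** All of the testing rules stand in the statistical methods section of the protocol article (item 20a).

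- For secondary endpoints, ANOVA or the H-test "by Kruskal-Wallis will be used for quantitative variables", while a Pearson chi-square "test will be performed for dichotomous or categorical variables".
- An earlier sentence in the same section names both tools together: Pearson chi-square and the H-test "by Kruskal-Wallis will be used for any assessment of differences between the three groups".
- A further sentence sends variables measured at several timepoints to repeated-measures ANOVA, Friedman or a mixed effects model.
- Ordinal variables appear once, in the sentence on describing demographic and clinical characteristics, which "will be presented as percentage in case of ordinal variables".
- Apart from the primary comparisons, a p-value "< 0.05 will be considered statistically significant".

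The secondary outcomes list includes "Postoperative and 30-day Acute Kidney Injury (according to AKIN score". The postoperative procedures section defines AKIN "through a stratification of renal damage in three stages", so with no injury there are four ordered levels. No AKI rate, stage distribution, effect size or power is given for this outcome. The trial design section calls the trial exploratory.

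**The concern.** A Pearson chi-square on three arms by four stages returns the same p-value if the stage columns are shuffled. It therefore cannot use the fact that stage 3 is worse than stage 2, and 2 worse than 1. It also spreads its sensitivity over (3−1)×(4−1) = 6 degrees of freedom, where a test for a shift between three arms needs 3−1 = 2. A significant result would not by itself say that one arm had worse kidney injury.

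AKI is named in the background as a consequence of renal hypoperfusion, and it is a secondary objective both after surgery and at 30 days. An order-respecting test, Kruskal-Wallis, is already in the plan but is assigned to quantitative variables. What is at stake is the sensitivity and readability of one secondary comparison. Validity is not at stake: type I error is about 5% for either test.

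**Working it through.** **1. The plan's own figure.** The only sample size given is for the primary endpoint: SD 0.7, difference 0.19, alpha 0.01667, power 80%, Mann-Whitney. Taking the test as two-sided, 2 × (2.394 + 0.842)² × (0.7/0.19)² ≈ 285 per group. Multiplying by π/3 for Mann-Whitney under normality gives about 299, against 300 stated. Dropout: 300/0.9 ≈ 333. So 300 and 333 per arm are sound inputs for what follows. There is no AKI figure to reproduce.

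**2. Assumed inputs.** These are not in the article: control-arm any-AKI rate, split across stages, and a proportional-odds effect in one or both other arms. Alpha is 0.05 (item 20a) and allocation 1:1:1 (trial design section).

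**3. Where the loss comes from.** Take control stages 75/18/4/3%, odds ratio 0.6 in one arm, 333 per arm. The shifted arm becomes 83.3/12.3/2.5/1.8%. With p the stage share in an arm and m its mean over arms:

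- Pearson, 6 df: λ = 333 × Σ(p−m)²/m = 333 × (0.00595 + 0.01323 + 0.00429 + 0.00355) ≈ 9.0. Critical value 12.59, power about 59%.
- Kruskal-Wallis, 2 df: arm mean ridits are 0.514, 0.514 and 0.472, with ridit variance 0.0438. λ = 333 × (2 × 0.01404² + 0.02807²)/0.0438 ≈ 9.0. Critical value 5.99, power about 77%.
- Any AKI yes/no, 2 df: rates 25%, 25%, 16.7%, mean 22.2%. λ = 333 × 0.00463/(0.2222 × 0.7778) ≈ 8.9, power about 77%.

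The signal λ is nearly identical for all three tests. The loss comes from the four extra degrees of freedom.

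**4. Simulation over a range** (20,000 trials per row, tie-corrected Kruskal-Wallis, 333 per arm, one arm shifted):

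| Control stages 0/1/2/3 (%) | Odds ratio | Pearson 6 df | Kruskal-Wallis | Yes/no chi-square |
|---|---|---|---|---|
| 80/14/4/2 | 0.7 | 26% | 41% | 40% |
| 80/14/4/2 | 0.6 | 50% | 70% | 70% |
| 75/18/5/2 | 0.7 | 31% | 48% | 48% |
| 75/18/5/2 | 0.6 | 60% | 79% | 78% |
| 75/18/5/2 | 0.5 | 87% | 96% | 96% |
| 70/20/7/3 | 0.7 | 36% | 54% | 54% |
| 70/20/7/3 | 0.6 | 68% | 85% | 84% |
| 70/20/7/3 | 0.5 | 93% | 98% | 98% |

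With any AKI of 15–35%, odds ratio 0.6–0.7 in one or both other arms and 300–333 per arm, the gap is about 11–20 points. It shrinks for weak effects (13% against 20% at odds ratio 0.8 in both other arms, 75/18/5/2, 300 per arm) and for strong ones (the 0.5 rows). With no effect, both tests reject about 5% of the time.

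**5. The case that goes the other way.** Any-AKI rate held fixed, 300 per arm:

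| Arms (stages 0/1/2/3, %) | Pearson 6 df | Kruskal-Wallis |
|---|---|---|
| 70/20/7/3; the other two 70/25/4/1 | 65% | 7% |
| 70/20/7/3 in two; one 70/15/10/5 | 48% | 7% |
| 75/20/4/1 in two; one 75/16/5/4 | 68% | 6% |

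In these tables the ranks are dominated by the large group without AKI, whose share does not change.

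**The case against.** The strongest reply is that the article never says which test AKIN gets. Three other readings are open:

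- The general sentence leaves Kruskal-Wallis available for any three-group comparison.
- AKI is assessed twice, so the repeated-timepoint sentence could apply.
- AKIN may serve only to define an AKI event, and a yes/no outcome properly takes chi-square with no loss.

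This stands to the extent that the chi-square assignment is an inference. A reader might infer that the article prescribes a 6-df test for AKIN; it does not say so. The ordinal-variables phrase does not fill the gap either, because it concerns descriptive presentation. Still, none of the three readings names an order-respecting between-arm test for AKIN stage. The general sentence lists tools that the later sentence then allocates. Friedman is a within-patient test and does not compare arms. Nor is yes/no stated for AKI, although the same outcomes list does mark neurological dysfunction as dichotomous.

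It can also be said that a condensed article may leave the test for each outcome to a fuller document. That would answer a complaint of silence. Here the article does fix a rule by variable type, and the rule fits ordered outcomes badly.

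Finally, the rank test is not uniformly better. Step 5 shows a loss of roughly 40–60 points for Kruskal-Wallis when only severity among injured patients changes, even when that change is a consistent worsening. This stands in full: the choice depends on the alternative the investigators expect.

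**Conclusion.** The point holds in a limited form. The plan splits secondary tests into quantitative and dichotomous-or-categorical and gives ordered outcomes no order-respecting test. On the natural reading, AKIN stage would be compared by an order-blind 6-df chi-square. Under an assumed moderate proportional-odds shift this costs roughly 11–20 points of power against Kruskal-Wallis.

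A reader might go further in two ways that the document does not support. One is to treat 11–20 points as a known loss: every rate and effect behind it is assumed, it vanishes under a yes/no analysis, and its sign changes under a severity-only effect. The other is to carry the figure over to the modified Rankin Scale. The outcomes list has that scale scored only after permanent neurological injury, so calculations on 300–333 patients per arm do not describe it.

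The chi-square is a valid test, the outcome is secondary, and the trial calls itself exploratory. This is a low-cost improvement; the primary analysis and the sample size are untouched.

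**What to change.** In the statistical methods section (item 20a), limit Pearson chi-square to dichotomous and unordered variables. Add that AKIN stage (0–3) at each timepoint is compared between arms by the Kruskal-Wallis test already in the plan, or by a proportional-odds model with arm as a factor, which also yields an odds ratio. If the investigators mean AKI as an event, declare it yes/no and keep chi-square. In either case, tabulate stage percentages by arm.

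The cost is one sentence and no new data. Recruitment is expected to run to 31/12/2026, so the wording can be settled before analysis. The statistical price is lower sensitivity to non-ordered stage changes and to changes in severity alone. The tabulated percentages would show such a pattern but would not test it. If a severity-only effect is thought plausible, that should be weighed before the test is fixed.
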